# Efficacy of antiviral drug AV2 in the treatment of human papillomavirus-associated precancerous lesions of the uterine cervix: A randomized placebo-controlled clinical trial in Kinshasa, DR Congo. (KINVAV study)

**DOI:** 10.1016/j.conctc.2017.09.008

**Published:** 2017-09-28

**Keywords:** Human papillomavirus, Precancerous lesions, Uterine cervix, Antiviral, Randomized clinical trial, Democratic Republic of the Congo

## Abstract

**Background:**

Cervical Cancer (CC) is a major public health problem in DR Congo; the high incidence of CC is due to the inexistence of effective screening programs based on cytology and/or HPV detection followed by appropriate treatments. This situation highlights the need to implement efficacious and inexpensive treatment methods. This study aims at evaluating the efficacy of a topical antiviral drug named AV2^®^ as a treatment for HPV-associated lesions of the cervix.

**Methods:**

Women will undergo cytology sampling, HPV testing and Visual inspection of the cervix after application of 5% acetic acid (VIA). VIA-positive women will be randomized to one of two groups to receive treatment by either AV2^®^or placebo. They will undergo control examinations after two months and after six months. In case of persistent lesions on VIA, treatment by cryotherapy will be done. The primary outcomes will be the change of lesions, the clearance of HPV DNA, and the correlation of the two 2 months after treatment with AV2^®^.

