### Outcomes

2.8

-The primary outcome will be the change of lesions 2 months after randomization.

Change of lesions will be defined as regression or progression of the size of the lesion seen on VIA. Regression can be partial or complete when there is a total disappearance of the lesion also called remission. On cytology, regression will be defined as improvement from high-grade to low-grade CIN and remission will be defined as improvement from any grade of CIN to no CIN.

-The secondary outcomes will be:The secondary outcomes will be•Clearance of HPV at 2 months post-randomization,•Correlation between change of lesions change in HPV DNA at 2 months post-randomization,•Change in HPV viral particle load 6 months post-randomization.-The tertiary outcome will be the number of patients with adverse effect.

An adverse effect (AE) will be defined as any unfavourable and unintended sign, symptom, or disease temporally associated with the use of the product administered. A causality assessment of the AEs will be done in accordance with the guidelines of the WHO–Uppsala Monitoring Centre.

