### Sample size

2.9

Assuming a lesion regression rate of 50% in the non-interventional group and 70% in the antiviral drug group at 2 months post-treatment, a minimum sample size of 163 patients is needed to show with 95% power a difference between both groups. To allow for up to 10% drop-outs or unevaluable patients, we will recruit at least 190 patients in each arm. We expect 20% of the women to be HPV positive, of whom 10% with and 10% without lesions, indicating that over 1900 women will have to be enrolled to obtain the required sample size.

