### Statistical analyses

2.10

Data will be double-entered and cleaned in EpiInfo (version 6.04 b, Centers for Diseases Control and Prevention). Proportions will be compared using the x^2^ or Fisher's exact tests (when required). Student's *t*-test will be used for continuous variables. A Mc Nemar or paired *t*test will be used for within-patient comparisons where approriate. Non-normally distributed variables will be transformed, or nonparametric tests (Wilcoxon or Kruskal-Wallis) will be used. Stepwise multivariate analyses will be performed, and all possible interactions up to order 2 will be tested. All reported *P* values will be 2-sided. For all statistical analyses a *P* value of ≤0.05 will be considered as statistically significant.

All analyses will be performed using the STATA statistical analysis software packages (Version 12; Stata Corp, Lakeway, College Station, Texas, USA).

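### The abstract names three primary outcomes where section 2.8 names one; the abstract should be aligned with sections 2.8 and 2.9

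*Protocol article*

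**What the plan says.** All of the text concerned is in the protocol article.

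- **Abstract, Methods:** "The primary outcomes will be the change of lesions, the clearance of HPV DNA, and the correlation of the two 2 months after treatment". Three outcomes carry the label primary.
- **Section 2.8, Outcomes:** "The primary outcome will be the change of lesions 2 months after randomization". The secondary list then contains "Clearance of HPV at 2 months post-randomization" and "Correlation between change of lesions change in HPV DNA at 2 months post-randomization". The two outcomes that the abstract promotes are therefore explicitly ranked below lesion change.
- **Section 2.9, Sample size:** the calculation uses one endpoint: "Assuming a lesion regression rate of 50% in the non-interventional group and 70% in the antiviral drug group at 2 months post-treatment". It gives no rate for HPV clearance and no size for the correlation.
- **Section 2.10, Statistical analyses:** P "values will be 2-sided", and a P "value of ≤0.05 will be considered as statistically significant". This threshold is given for all analyses alike.

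The time origin also varies. The abstract and section 2.9 count two months from treatment; section 2.8 counts them from randomisation.

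**The concern.** The primary outcome decides whether a trial is read as positive. Suppose that lesion change shows no difference and HPV clearance gives P < 0.05. A reader holding the trial to its abstract could call it positive; a reader of section 2.8 would call it negative.

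The two results could diverge. Lesions are read on VIA, which the Discussion calls subjective, while HPV is a laboratory PCR result. With both rankings in print, the choice between them could be made after the results are known, and that raises the chance of a false claim of efficacy.

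This is not a detail that a condensed article leaves to an analysis plan. It is one article giving two incompatible rankings of the same outcomes.

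**Working it through.** **1. Which ranking does the sample size support?**

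Inputs from section 2.9: p₁ = 0.50, p₂ = 0.70, power 95%. From section 2.10: two-sided 0.05. Equal arms are inferred from the plan to recruit at least 190 in each.

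Without continuity correction:

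n₀ = [z₀.₉₇₅ √(2 p̄ q̄) + z₀.₉₅ √(p₁q₁ + p₂q₂)]² / (p₂ − p₁)²

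= [1.960 × √0.48 + 1.645 × √0.46]² / 0.04 ≈ 152.95, rounded up to 153 per arm.

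With continuity correction:

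n = (n₀/4) × [1 + √(1 + 4/(n₀ × 0.20))]² ≈ 162.8, rounded up to **163 per arm**.

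This matches the stated figure exactly. Allowing for 10% drop-out, 163/0.9 = 181.1, so 182 per arm, and the planned 190 covers it. The trial is sized for lesion regression as a single endpoint with the whole 0.05, which is the ranking in section 2.8.

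**2. Error rate if the abstract's list is used and one success is enough**

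Only lesion change and HPV clearance compare the arms. The correlation between them is an association, not a treatment effect, so it is not counted here.

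- Two independent tests at 0.05: 1 − 0.95² = 1 − 0.9025 = **0.0975**.
- Upper bound under any dependence: 2 × 0.05 = **0.10**.
- Positively correlated test statistics (simulated; the correlations are assumptions, since the article gives none): about 0.091 at 0.5 and about 0.078 at 0.8.

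**3. If all primary outcomes must succeed**

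The error rate does not inflate, but power cannot exceed that of the weakest outcome. With 163 evaluable per arm, power for lesion regression alone is 96.1% (no continuity correction). Joint power cannot be calculated, because no HPV clearance rates are given.

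**4. What it would cost to keep two between-arm primaries with the error rate controlled**

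Bonferroni gives 0.05/2 = 0.025 each. The same formula then needs 188 evaluable per arm with continuity correction, and 188/0.9 = 208.9, so 209 recruited. Without the correction it needs 179, and 179/0.9 = 198.9, so 199 recruited. Both exceed 190. The shortfall in power is modest: with 190 × 0.9 = 171 evaluable per arm, power at 0.025 is 94.1% (no continuity correction).

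**The case against.** The strongest reply is that the abstract is one outlying sentence. Section 2.8, the detailed statement of outcomes, and section 2.9 both point to lesion change as the only primary outcome, and a reader following the methods would not call the trial positive on HPV clearance alone. This stands. A reader might infer that the article leaves the meaning of a positive trial wholly open. It does not, because its operative sections agree. What remains is that the abstract, the part most widely read, says something else.

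A reader might also count three tests and quote 1 − 0.95³ = 14.3%, with a bound of 15%. The article does not support that as an inflation of efficacy claims, because a correlation between lesion change and HPV change cannot show that one arm did better. Independence is doubtful too: section 2.7 postulates that lesions regress because the virus is deactivated, which suggests positively related tests and a rate below 9.75%.

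Any inflation also depends on one success being enough, and the abstract does not say so.

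The lack of a multiplicity adjustment or testing order in section 2.10 is not itself a fault. With one primary outcome none is needed for the main claim, and the handling of secondary outcomes is commonly left to the analysis plan. Testing HPV clearance only after a significant primary result, or calling the correlation exploratory, would be preferences that go beyond removing the contradiction.

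The varying time origin is minor. Section 2.3 schedules a single two-month recall for all randomised women, so there is no second assessment to choose from.

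**Conclusion.** The contradiction is real: the abstract has three primary outcomes, and section 2.8 has one, with the other two secondary. The sample size agrees with section 2.8.

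If the abstract's list governed and either between-arm outcome sufficed, the false-positive rate would be 9.75% under independence, at most 10%, and about 7.8% to 9.1% at assumed correlations of 0.8 to 0.5, against 5% for the single primary. If all had to succeed, the cost would be power, by an amount that the article does not allow one to calculate. Neither rule is stated.

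The problem is limited to an inconsistent abstract. The sample size and the significance level are sound for the ranking in section 2.8. It still deserves correction, because it leaves open a choice of primary outcome after the results are known.

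**What to change.** Change the abstract to match sections 2.8 and 2.9:

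- one primary outcome, lesion change at the two-month visit, compared between arms at two-sided 0.05;
- HPV clearance and the lesion–HPV correlation as secondary outcomes, with a statement that neither can by itself make the trial positive;
- one time origin, post-randomisation, in the abstract and in sections 2.8 and 2.9.

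The trial status is given as recruiting, so the correction should be dated and on record before outcome data are unblinded.

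The change is one of wording. The sample size stays at 163 evaluable and at least 190 recruited per arm, and alpha stays at 0.05. The only loss is HPV clearance as an alternative route to a positive claim. The edit settles the ranking of outcomes only; it does not decide how the VIA and cytology definitions of lesion change in section 2.8 are to be combined.

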**Conclusion:**

This study is the first large-scale study in Africa to evaluate systematically the efficacy and safety of a topical antiviral drug for the treatment of HPV— associated lesions of the cervix. Its findings will direct the planning of suitable algorithms for CC screening and treatment.

**Clinical trial registration:**

ClinicalTrials.gov – Unique identifier: NCT02346227, registered on November 8, 2014.

## Introduction

1

Cervical cancer (CC) is the third most common cancer in women worlwide with an estimated 530 000 new cases per year. It is the most common cancer in women of Low and Middle Income Countries (LMICs) [1].

In the Democratic Republic of the Congo (DRC), 18.85 million women, aged 15 years and older are at risk of developing CC. Current estimates indicate that every year 6024 women are diagnosed with cervical cancer and 4719 die from the disease [2].

The link between human papillomavirus (HPV) infection and CC is well established [3]. HPV infection is implicated in 99.7% of CC cases worldwide [4], [5]. When HPV infection persists in the cervix, it can induce changes which constitute the precancerous lesions of the cervix (PLC), also called dysplasia or cervical intraepithelial neoplasia (CIN)·CIN is asymptomatic and progresses to CC over a prolonged period of time (7–20 years). CC can be prevented by screening and treatment of CIN in asymptomatic women. Cytology is considered as the standard CC screening method but is not feasible in LMICs due to its high cost, lack of adequate infrastructure or qualified cytotechnicians. Therefore, visual inspection of the cervix after application of 5% acetic acid (VIA) is recommended as a screening tool in low-resource settings with no acces to HPV testing or cytology screening. It has limited specificity but a high sensitivity, is cost-effective and provides immediate results [6], [7].

Sauvaget et al. performed meta-analyses with different categories of studies to provide an updated estimation of the accuracy of visual inspection with acetic acid (VIA) in detecting true disease. The reference category consisted of 26 studies in which VIA was performed on asymptomatic women who all underwent confirmatory testing and in which the disease threshold was cervical intraepithelial neoplasia grade 2. They reported an 80% sensitivity (range, 79%–82%) and a 92% specificity (range, 91%–92%) for VIA. Study region, capacity of screener, or size of the study population did not modify VIA accuracy. In conclusion, it was shown that screening for precancerous and cancerous cervical lesions using VIA is a simple, low-cost, and efficient alternative to cytologic testing in low-resource areas. The more the severity of disease, the more sensitive and specific is VIA in detecting the disease [8].

In another meta-analysis by Sauvaget, Cryotherapy was shown to be an effective, safe, and acceptable treatment for CIN. Actually, on a equivalent of 28,827 cases of treated CIN, Cryotherapy achieved cure rates of 94.0% for CIN1, 92.0% for CIN2, and 85.0% for CIN3 [9].

Of all available and effective treatments of CIN, cryotherapy seems the most appropriate for LMICs, but is still hampered by major logistical problems such as unavailability of refrigerant gas. These feasibility issues highlight the need for a low-cost and minimally invasive method of treating CIN in LMICs [7].

Recently, an antiviral drug called Antiviral 2 (AV2^®^, Cesa Alliance, Luxembourg) made of natural essential oils was developed and preliminary results suggest it to be effective in clearing or reducing the size of PLC related to HPV [10]. The Food and Drug Administration (FDA) approved its organic compounds (carvone, eugenol, geraniol, and nerolidol). These combined compounds have a broad spectrum anti-viral effect, both topically and orally [11] and AV2 may regress cervical lesions due to deactivation of the virus.

In a recently published phase 2 clinical trial study conducted by Martinez et al. at Hospital de la Familia, in Juarez, Mexico, efficacy of AV2^®^ in the regression of cervical lesions diagnosed at colposcopy was compared to placebo in 50 women over the age of 18. The results showed that the application of AV2^®^ yielded a reduction of more than 50% of lesion size for 21 out of the 28 (75%) patients who received the active treatment, versus 0% for the comparable placebo pool. At the other end of the scale, only 2 (7%) participants in the AV2^®^ group failed to respond positively compared to 80% of participants in the placebo group [12]. Medical treatment of precancerous lesions of the cervix with AV2^®^ could offer minimally invasive treatment with minor morbidity and time constraints.

## Methods/design

2

### Study design

2.1

The present study is a double-blind randomized placebo-controlled clinical trial. It will include 400 patients in a health centre in Kinshasa, DRC: Centre Hospitalier du Mont-Amba. It is estimated to last 56 weeks considering final data collection for primary outcome measurements.

### Patients

2.2

Inclusion criteria: The targeted population is all sexually-active women, aged at least 25 years old and who will give their informed consent to participate in the study.

The reason for this target population is based on the natural history of HPV infection. HPV is acquired at the onset of sexual activity which occurs at around 15 years of age. Its prevalence is very high at a younger age and is often transient because most women will spontaneously eliminate the virus after some years. When it persists, HPV infection can take in average 10 years to lead to CC. Thus, testing is projected to start 10 years later after sexual debut in this case at 25 years old onward.

Exclusion Criteria: Pregnant, breastfeeding and post-partum women will not be accepted in the study. In case of suspected or diagnosed cervical cancer, the women will be referred in a tertiary hospital for the proper management. Other exclusion criteria include: previous cervical surgery, medical history of any severe diseases, intake or application of other antivirals, known or suspected allergic or adverse response to the investigational product or its components and women who are unable to follow the study protocol.

### Procedures and follow-up (Fig. 1)

2.3

Prior to the start of the study, a basic training of the doctors and nurses involved will be organized. This training will encompass Good Clinical Practice (GCP), collection of liquid-based cytology sample with cytobrushes, and VIA and cryotherapy procedures.

Women aged 25 and over will be invited to participate in a community cervical cancer screening programme. After giving their informed consent, eligible women will be examined by a trained doctor. The procedure will be performed while the woman lies in the lithotomy position on the examination table. After the cervix is exposed by a speculum inserted in the vagina, the doctor will collect a LBC specimen using the Thinprep PreservCyt solution^®^ (Hologic, Marlborough,USA), immediately after LBC sampling, VIA will be performed. Its results will be reported according to the WHO criteria and will serve for randomization. The results for LBC and HPV testing will not be available at this moment.

VIA-negative women will not be randomized and will receive no treatment. VIA-positive women will be randomized to one of two groups to receive either AV2^®^ or placebo. All randomized women will be followed-up and recalled after two months for repeat LBC and VIA. Women remaining positive on VIA at this stage will be treated by cryotherapy.

At six months' follow-up, women will be assessed in the same manner regarding VIA and LBC. The study will end at this stage. At each stage, the examinators will be blind to the previous results concerning the patient. At the end of the study, All women who will test positive for cervical lesions or HPV will be properly treated according to standard protocols and resources.

### Randomization and blinding

2.4

VIA positive women will be randomized in a block wise manner, without stratification, to one of two treatment arms as shown in Fig. 1. Patients and study investigators will have no knowledge of the treatment arm allocation. To maintain blinding, active drug and placebo glass containers will be identical in appearance and scent. Patients and investigators will be unblinded only in the event of a suspected serious adverse reaction.

**Fig. 1 fig1:**
[figure not shown]
Study design.

### Visual inspection of the cervix with acetic acid

2.5

VIA involves the painting of the cervix with 5% acetic acid and the observation of the color change 1 min after. The most common form of reporting the VIA test outcome involves negative and positive categories, depending upon the absence or presence of acetowhite lesions and clinical signs of invasive cancer. A positive test is generally based on the detection of well-defined, densely opaque acetowhite lesions in the transformation zone closer to the squamocolumnar junction. The criteria for a negative test includes one or more of the following: no acetowhite lesions, faint ill-defined translucent acetowhite lesions, endocervical polyps, nabothian cysts, dot-like acetowhite lesions, acetowhite lesions far away from the transformation zone and a prominent squamo-columnar junction.

### Methods for LBC samples

2.6

It is not possible to perform HPV testing locally as there are no laboratory facilities in DRC allowing this. Laboratory examinations will be done at the HPV and STIs Training Centre for Africa, Sefako Makgatho Health Sciences University, Pretoria, South Africa. To ensure quality, all the samples will be re-examined at Algemeen Medisch Laboratorium (AML) in Antwerp, Belgium.

From a single LBC specimen collected in the ThinPrep test vial containing the PreservCyt^®^ solution, both cytology and HPV testing will be performed. HPV testing in this study will encompass both HPV detection and HPV genotyping as well as HPV viral particle load. Cytology results will be reported according to the 2001 Bethesda system terminology.

Sample collection

The HPV and STIs Training Centre for Africa will receive Thinprep vials with 10 ml of the cervical sample. The samples will be stored at room temperature between 15 °C and 30 °C in a store room. The level 2 safety hood is set up and prepared by cleaning with alcohol followed by DNASe away for decontamination. The vials will be moved to dirty area (extraction room) for preparation. The pipettes will also be cleaned with alcohol and DNASe away for decontamination. The 2 ml tubes will be labeled according to the sample number on the ThinPrep vials. A 1000 μl pipette will be used to remove 2 ml of sample from the ThinPrep vials into the 2 ml test tubes for HPV testing avoiding any spillage or aerosol. The ThinPrep vials will be then filled to the ThinPrep vial mark (10 ml) with Preservcyt solution to prepare for cytology slide processing. The ThinPrep vials will then be capped and stored at room temperature until processing of the cytology slides on ThinPrep T5000 system.

#### Liquid-based cytology

2.6.1

Preparation of the cytology slides will be performed from the cervical samples in ThinPrep Preservcyt^®^ solutions using the ThinPrep T5000 cytology system. Labeled slides with corresponding number on the Vial together with a filter and the vial are placed on the carousel for processing. Once prepared, the slides will be stained and covered with cover using entelen. After staining, the slides will be screened by a qualified and trained cytotechnologist and reviewed by Pathologist. All the results will be reported on a form using the vial number only as identifier.

#### HPV testing

2.6.2

We will use the Abbott system. The Abbott RealTime High Risk HPV is a qualitative, multiplex real time PCR for the detection of DNA from 14 High Risk HPV genotypes 16, 18, 31, 33, 35, 39, 45, 51, 52, 56, 58, 59, 66, and 68 in clinical specimens, typing of HPV 16 and/or HPV 18, single and mixed infections (Abbott Molecular, Wiesbaden). An endogenous human beta globin sequence is detected as sample validity control for cell adequacy, sample extraction and amplification efficiency. Two external controls (negative and positive controls) are included in every run. The viral load will be expressed as the number of HPV copies per million of normal human cells.

